**Fig. 1 Fig1:**
[figure not shown]
Study design SCP: stable chest pain; CCS: chronic coronary syndrome; CAD: coronary artery disease; ECG: electrocardiogram; NICE strategy: 2016 National Institute of Health and Care Excellence guideline-determined strategy; ESC strategy: 2019 European Society of Cardiology guideline-determined strategy; MACE: major adverse cardiovascular event; CCTA: coronary computed tomography angiography; RF-CL: risk factor-weighted clinical likelihood; PTP: pretest probability

### Enrollment and screening

Subjects will be enrolled competitively from five major cardiac centers recognized as tertiary A level (Tianjin Chest Hospital, Tianjin First Central Hospital, Beijing Chaoyang Hospital, Tianjin Second Teaching Hospital of Tianjin University of Traditional Chinese and Hebei Petrochina Central Hospital) in Beijing-Tianjin-Hebei region, which has more than 100 million population. The total annual number of patients presenting with SCP suggestive of CCS and referred to CIT in these high-volume sites is more than 30,000 and 20,000, respectively. Subjects are considered eligible for inclusion if they suffer SCP suggestive of CCS, are more than 30 years of age, and willing and able to give informed consent. Eligible subjects are clinically stable, have no history of CAD and will undergo routine electrocardiogram (ECG) and echocardiography according to the latest guideline [3, 4]. Trained research nurses introduce the trial to subjects and investigators are advised not to randomize subjects who expressed a clear preference for undergoing CIT or not during the informed consent process. More details about inclusion and exclusion criteria are listed in Table 1.

**Table 1 Tab1:** Inclusion and exclusion criteria

Inclusion criteria	1. SCP or equivalent^a^ suggestive of CCS and clinically stability
	2. No history of CAD (prior myocardial infarction, CR or any CAD documented by previous CIT)
	3. Age ≥ 30 years
	4. Willing and able to provide informed consent
Exclusion criteria	1. Prior CIT within 1 year prior to randomization
	2. Clinically instability (e.g. cardiogenic shock, ACS, severe arrhythmias or NYHA III or IV heart failure)
	3. Non-sinus rhythm
	4. Concomitant participation in another clinical trial
	5. Complex structural heart disease
	6. Non-cardiac illness with life expectancy < 2 years
	7. Allergy to iodinated contrast agent
	8. Estimated glomerular filtration rate < 60 ml/min/1.73m^2^ within 90 days
	9. Body mass index > 35 kg/m^2^
	10. Expressing a clear preference for undergoing CIT or not
	11. Pregnancy

CIT: cardiac imaging testing; CCS: chronic coronary syndrome; SCP: stable chest pain; CAD: coronary artery disease; ECG: electrocardiogram; NCCT: non-contrast CT; ACS: acute coronary syndrome; CR: coronary revascularization

a: The followings are not SCP:

1) First appearance within the last 48 h or Canadian Cardiovascular Society Angina Grading Scale (CCSAGS) Class IV

2) Progressive with at least 1 CCSAGS Class to at least CCSAGS Class IV

3) Now at rest for at least 30 min

### Baseline clinical data

Baseline characteristics are defined and collected as described previously [16, 18, 22]. Hypertension is defined as blood pressure of ≥ 140/90 mmHg or the use of anti-hypertension medication. Hyperlipidemia is defined as total cholesterol of ≥ 220 mg/dL, low-density lipoprotein cholesterol of ≥ 140 mg/dL, fasting triglycerides of ≥ 150 mm/dL or receiving treatment with oral lipid-lowering agents. Diabetes is defined as fasting glucose levels over 7 mmol/L or treatment currently with either diet, oral glucose lowering agents or insulin. Smoking is defined as current smoking or smoking in past 6 months. Abnormal ECG is defined pathological Q waves or ST-segment and T wave abnormalities in at least two adjacent leads. A family history of premature CAD is defined as diagnosis of the disease in a male first-degree relative before 55 years of age or in a female first-degree relative before 65 years of age. Typical angina is defined as having 3 characteristics: (1) substernal discomfort of characteristic quality, (2) precipitated by physical exertion or emotion, and (3) relieved with rest or nitroglycerin within 10 min. Atypical angina is defined as having 2 of the 3 definition characteristics. Nonanginal chest pain is characterized as chest pain or discomfort that meets 1 or 0 of the 3 definition characteristics [23].

### Randomization and blinding

After collection of baseline clinical data, eligible subjects will be randomized (in blocks of 2) sequentially 1:1 to start double-blind diagnostic strategy with 1 of 2 regimens: NICE and ESC. The computerized randomization list is generated independently by a statistician from the statistical and data coordinating group who will not participate rest of the study. Both investigators and subjects are blinded to the allocation process until the end of trial (sequentially numbered, opaque, sealed envelope will be used to conceal allocation). Once the subject is ready for randomization, the corresponding envelope will be opened by the independent strategy assignment expert panel consisting of cardiologists who will not participate rest of the study. The expert panel determine whether the subject should be referred to CCTA according to the given diagnostic strategy (see below) and only send the final recommendation about referral or deferral of CCTA to the physician and subject.

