### Diagnostic strategies

For a subject in high risk group according to each strategy, CCTA should be referred as the first-line CIT and other CIT, including noninvasive functional testing (NFT) and invasive coronary angiography (ICA), will be considered as an alternative. In both diagnostic strategies, subjects determined to be at low risk will be referred to optimal medication treatment (OMT) with no immediate CIT. The decisions regarding OMT will be done at discretion of the referring physicians according to recent primary prevention guidelines [24, 25], and is not a part of the study protocol. Thus, in cases where symptoms don’t resolve with maximum OMT, additional cardiac or non-cardiac diagnostic testing could be pursued as an escalation of the diagnostic strategy. Based on current SCP guidelines [3–5] and results of proposed researches [11–17], details of risk groups are illustrated in Fig. 1; Table 2 and as follows:

**Table 2 Tab2:** Low and high risk groups according to NICE and ESC strategy

	NICE strategy	ESC strategy
Low risk group	Both normal ECG and nonanginal chest pain	ESC-PTP ≤ 5%, or both 5%< ESC-PTP < 15% and RF-CL < 15%
High risk group	Typical and atypical angina, or nonanginal chest pain with abnormal ECG	ESC-PTP ≥ 15%, or both 5%< ESC-PTP < 15% and RF-CL ≥ 15%

ECG: electrocardiogram; NICE strategy: 2016 National Institute of Health and Care Excellence guideline-determined strategy; ESC strategy: 2019 European Society of Cardiology guideline-determined strategy; RF-CL: risk factor-weighted clinical likelihood; PTP: pretest probability

According to NICE strategy, subjects with nonanginal chest pain and normal ECG are classified into low risk group. Subjects with typical and atypical angina or nonanginal chest pain with abnormal ECG are classified into high risk group [5].

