For each subject, ESC-PTP is calculated using age, sex and type of chest pain according to 2019 ESC guideline for the diagnosis and management of CCS [3] and RF-CL is calculated using age, sex, type of chest pain, hypertension, dyslipidemia, diabetes, smoking and family history of CAD based on the publication of Winther et al. [11], respectively. According to ESC strategy, subjects with ESC-PTP ≤ 5% are classified into low risk group and ones with ESC-PTP ≥ 15% are classified into high risk group [3]. For subjects with ESC-PTP of 5-15%, ones with RF-CL ≥ 15% are classified into high risk group and ones with RF-CL < 15% are classified into low risk group. The cut-off of 15% for RF-CL is chosen because RF-CL < 15% was associated with an extremely low prevalence of obstructive CAD and risk of clinical events [11, 16].

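### Fixed blocks of 2 let a site know the second allocation in a block whenever the referral advice reveals the first; how often depends on whether lists run per site or centrally

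*Protocol article*

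**What the plan says.** All references are to the protocol article.

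- **Randomization and blinding** fixes the scheme: "eligible subjects will be randomized (in blocks of 2) sequentially 1:1". It also says that "Both investigators and subjects are blinded to the allocation process until the end of trial". The safeguards are numbered, opaque, sealed envelopes and an independent panel that opens them, applies the assigned strategy, and will "only send the final recommendation about referral or deferral of CCTA to the physician and subject".
- The same section puts baseline collection before allocation: "After collection of baseline clinical data, eligible subjects will be randomized".
- **Diagnostic strategies** (text and Table 2) gives both rules. Under NICE, "subjects with nonanginal chest pain and normal ECG are classified into low risk group", and the high-risk group is "Typical and atypical angina, or nonanginal chest pain with abnormal ECG". Under ESC, "ESC-PTP is calculated using age, sex and type of chest pain", and for intermediate values "RF-CL is calculated using age, sex, type of chest pain, hypertension, dyslipidemia, diabetes, smoking and family history of CAD".
- **Enrollment and screening** describes competitive enrolment at five centres and tells investigators not to randomize subjects who state a definite wish for or against imaging.
- **Sample size** assumes a low/high split of 2:3 for NICE, and its calculation for ESC uses a high-risk share of 2/5.

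**The concern.** Two features combine. First, a 1:1 block of 2 has only two possible orders, NICE-ESC and ESC-NICE, so the second allocation carries no uncertainty once the first is known. Second, the advice can make the first known. A physician who holds the baseline data can work out what each rule would recommend. If one rule says refer and the other says defer, the advice received matches only one strategy. Sealed envelopes and a separate panel hide the paper, but they do not prevent this deduction.

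Allocation concealment is at stake. Several steps before randomization rest on site judgement: eligibility, whether a subject's preference about imaging is strong enough to exclude them, and the typing of chest pain, which feeds both rules. The primary endpoint requires a CCTA, so who enters each arm, and how their pain is typed, bears on it directly. A recruiter who expects a particular arm could, even without intent, enrol or classify the next subject differently.

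**Working it through.** **Inputs.** Block size 2, 1:1, N = 800, five centres. High-risk shares come from the Sample size section: NICE 3/5 = 60%, ESC 2/5 = 40%. The projected rates reproduce from these shares: 3/5 × 62% = 37.2% and 2/5 × 57% = 22.8%. (The printed NICE product shows 57% where 37.2% needs 62%; this does not affect the shares used here.) The stated power, more than 99%, also reproduces to rounding: 98.9% at 360 per arm and 99.4% at 400. Nothing below depends on it.

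**Step 1: how often the advice reveals the arm.** Let d be the proportion of subjects on whom the rules disagree. The article does not report d. The two shares bound it below: d ≥ |0.60 − 0.40| = 0.20, or 160 of 800. This minimum occurs if every ESC high-risk subject is also NICE high risk. If the rules were independent, d = 0.60 × 0.60 + 0.40 × 0.40 = 0.52. Both rules use chest-pain type, so positive association and a smaller d are plausible. I take 0.20 to 0.40 as the working range; values above 0.20 are assumptions.

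**Step 2: allocations known in advance.** An allocation is certain beforehand when all B/2 places of the other arm in its block have been revealed. In a random block of size B, the number of places left once one arm has filled averages B/(B/2 + 1). All B/2 members of the filled arm must be discordant, which has probability d^(B/2). The share of allocations certain in advance is therefore

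d^(B/2) / (B/2 + 1),

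that is, d/2 for B = 2, d²/3 for B = 4 and d³/4 for B = 6. For an equal mix of 4s and 6s it is (4·d²/3 + 6·d³/4)/10. The observer is assumed to know the block boundaries, which favours prediction.

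**Step 3: list structure.** If one list serves five equal sites, the revealed subjects must also belong to the site enrolling next. Each then contributes a factor 1/5, so d is replaced by d/5.

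| d | Blocks of 2, list per site | Blocks of 2, one list | Mixed 4/6, list per site | Mixed 4/6, one list |
|---|---|---|---|---|
| 0.20 | 10% (80) | 2% (16) | 0.65% (5) | 0.02% |
| 0.30 | 15% (120) | 3% (24) | 1.6% (13) | 0.05% |
| 0.40 | 20% (160) | 4% (32) | 3.1% (25) | 0.09% |

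Counts are out of 800; the last column is under one subject throughout. Simulation agrees with every column. At d = 0.52 (independence), blocks of 2 give 26% (208) with lists per site.

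**Step 4: what block size cannot change.** A discordant subject's own advice reveals the arm whatever the block size, so at least a proportion d is unmasked. With blocks of 2 on a per-site list, a discordant partner reveals the other member as well, so the share eventually deducible is 1 − (1 − d)². At d = 0.20 this is 1 − 0.64 = 36%, or 288 subjects.

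**The case against.** The strongest reply concerns list structure. The article speaks of one randomization list and one panel, with sequential allocation and competitive enrolment across centres. That wording fits a central list at least as well as site lists. On a central list the site would also have to know that its subject was first in a pair and that its own next subject is next in the whole trial. This stands. A reader might infer that 80 to 160 allocations are certain to be compromised, but the document does not support that: those figures require one list per site, and 16 to 32 is itself an upper figure for a central list.

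A second reply is that bias in the endpoint has not been shown. This also stands. CCTA is read by a core laboratory blinded to other data, and events are adjudicated masked, so the exposure runs through selection and classification at entry and through later care decisions by physicians who can infer the arm. As an illustration on an assumed effect, suppose foreknowledge shifted the endpoint rate by 20 percentage points in every predictable subject of one arm. That arm would move 0.10 × 20 = 2 points at 10% predictability and 0.02 × 20 = 0.4 points at 2%. The planned difference is 37.2 − 22.8 = 14.4 points.

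Third, randomization already follows baseline collection, and chest-pain type is a three-item count. Both narrow discretion. Neither removes it, because a predicted arm is known before the next subject's baseline data are taken.

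Finally, a reader might take the absence of centre stratification as an error. It is not: a condensed article may leave it out, and it is a choice rather than a requirement.

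**Conclusion.** The weakness is real and follows from a stated rule. Blocks of 2 make the second allocation certain once the first is inferred, and the advice allows that inference for every subject on whom the rules disagree, at least 20% on the plan's own splits. Advance predictability is up to 10% to 20% of allocations with per-site lists and about 2% to 4% with a single list over five equal sites, for d from 0.20 to 0.40. These figures assume that recruiters know the block size (the article publishes it), can apply both rules, and can follow their position in the list.

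The conclusion is limited to weakened allocation concealment. It does not extend to biased endpoint reading, and the documents do not show that the primary comparison would be materially wrong. The unmasking of discordant subjects by their own advice is a separate matter: it comes with comparing two published rules whose output the physician must receive, and the description of blinding should say so.

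**What to change.** 1. For remaining allocations, replace blocks of 2 with larger permuted blocks of randomly varying size, for example 4 and 6, and keep the sizes out of anything the sites see. Even if the sizes were known, advance predictability falls to about 0.6% to 3.1% with per-site lists, or 0.1% or less with a single list.
2. Have the panel open an envelope only after chest-pain type and ECG are recorded and locked. This prevents reclassification once the advice is out. It would not by itself stop prediction of the next arm, so it complements the first change.
3. State whether there is one list or one per site. Centre stratification is optional. If the list is now central, adding stratification gives back part of the gain: at d = 0.40, central blocks of 2 give 4.0%, site-stratified 4/6 blocks 3.1%, and central 4/6 blocks under 0.1%.
4. Qualify the double-blind description: the strategy label is withheld, but the arm can be deduced where the two rules disagree.

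The cost is a new list, a short amendment and a possible imbalance of a few subjects, which is negligible with 400 per arm.

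### The expert panel opens the allocation envelope before deciding on CCTA referral, so the sequence leaves room for arm-aware classification, although none is shown

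*Protocol article*

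**What the plan says.** All from the protocol article.

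- **Order of steps (Randomization and blinding).** "After collection of baseline clinical data, eligible subjects will be randomized (in blocks of 2) sequentially 1:1". Then "the corresponding envelope will be opened by the independent strategy assignment expert panel consisting of cardiologists", who take no further part in the trial. Next, "The expert panel determine whether the subject should be referred to CCTA according to the given diagnostic strategy". The panel is to "only send the final recommendation about referral or deferral of CCTA to the physician and subject".
- **Who is blinded (same section).** "Both investigators and subjects are blinded to the allocation process until the end of trial". The panel is not named there, and it cannot be blind once it has opened the envelope.
- **Inputs (Baseline clinical data).** Chest pain type is a count of three characteristics. For the ECG: "Abnormal ECG is defined pathological Q waves or ST-segment and T wave abnormalities in at least two adjacent leads".
- **Rules (Diagnostic strategies, Table 2).** Under NICE, "subjects with nonanginal chest pain and normal ECG are classified into low risk group"; everyone else is high risk. The ESC strategy applies cut-offs to ESC-PTP and RF-CL. Both scores use chest pain type; neither uses the ECG.
- **Endpoint (Study endpoint).** The primary event is a CCTA in initial management that shows no obstructive CAD or is nondiagnostic.

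**The concern.** The refer/defer recommendation is the intervention. A subject who is deferred, and who follows that recommendation, has no initial CCTA and so cannot have the primary event. Blinded reading in the core laboratory and masked event adjudication come after this step and cannot undo a tilt introduced there.

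The rules are fixed, but two of their inputs need a reader. Judging whether discomfort has the characteristic quality decides the count of angina features. The definition of an abnormal resting ECG gives no size for the ST-segment or T-wave change, whereas the article's exercise ECG criterion does (1.5 mm). Under NICE, a single call on atypical versus nonanginal pain, or on a minor ECG change, can switch the recommendation. Under ESC, a chest pain call can also switch it by moving a score across a cut-off, but an ECG call cannot. If borderline calls were settled with the arm known, the arms could be sorted differently for reasons other than the strategies themselves, in a trial described as double-blind and confirmatory with a hypothesis that favours ESC.

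**Working it through.** **1. Order of steps.** Baseline data are collected, the subject becomes ready for randomization, the panel opens the envelope, the panel determines referral, and the recommendation is sent. The determination therefore follows disclosure of the arm. The text does not say that the panel re-grades pain type or ECG. It also does not say that these gradings are closed to the panel, or that the risk group is set before opening.

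**2. The plan's own figures (Sample size).**
- NICE: 3/5 × 62% = 37.2%. The printed product shows 57%, which would give 34.2%; the 62% in the same sentence reproduces the stated 37.2%. That is a separate matter.
- ESC: 2/5 × 57% = 22.8%.
- Planned difference: 37.2 − 22.8 = 14.4 points.
- Power at two-sided 5%: 99.4% with 400 per arm and 98.9% with 360 per arm (after 10% noncompletion), against a stated figure of more than 99%. The present point does not depend on this.

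**3. Illustration A: NICE subjects tilted toward referral.** Added points = share tilted × non-obstructive rate among them. The share is an assumption. For the rate, 62% is the plan's high-risk figure and 90% is an assumed upper value for borderline subjects.

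| Share tilted | Rate 62% | Rate 90% |
|---|---|---|
| 5% | 0.05 × 62 = 3.1 points | 0.05 × 90 = 4.5 points |
| 10% | 0.10 × 62 = 6.2 points | 0.10 × 90 = 9.0 points |

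For 5%, this is 3.1/14.4 = 22% to 4.5/14.4 = 31% of the planned difference, which becomes 17.5–18.9 points. A tilt the other way would shrink the difference instead.

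**4. Illustration B: no true difference.** Assume 360 analysed per arm, a 30% event rate in both arms, and that 60% of the subjects moved from referral to deferral in one arm would have had the event. A 5% shift lowers that arm by 0.05 × 60 = 3 points, to 27%.
- Pooled SE = √(2 × 0.285 × 0.715/360) = 0.0336
- Unpooled SE = √((0.30 × 0.70 + 0.27 × 0.73)/360) = 0.0336
- Upper tail: Φ((0.03 − 1.96 × 0.0336)/0.0336) ≈ 0.143; lower tail ≈ 0.002
- Rejection rate ≈ 14%, instead of 5%

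The same formula gives about 5.4%, 6.4% and 44% for shifts of 1%, 2% and 10%. With no reclassification it stays at 5%.

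**5. Block size.** In a 1:1 block of 2, the second allocation is always the opposite of the first. A panel that opens envelopes in sequence and knows the block size can predict the second subject of each block, that is 1/2 of subjects, or 400 of 800. Asking the panel to classify first and open afterwards would not blind it for that half.

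**The case against.** The case on the other side is substantial.

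- **The inputs precede randomization.** Chest pain type and ECG abnormality are defined baseline variables, collected before allocation by staff who do not know the arm. This stands, and it makes a large shift less likely.
- **The rule has no stated discretion.** Table 2 turns recorded inputs into a class, the panel is independent and takes no further part, and someone must know the arm to apply one of two rules. This stands in part. Knowing the arm is needed to select a class, but not to assign one.
- **This is a condensed article.** Form locking and panel procedures may sit in documents not shown. That is fair for the locking detail. The order, with opening first and determination second, is stated rather than omitted.

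A reader might go further and infer any of four things that the document does not support:

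- *That the primary comparison is biased.* No text says that the panel re-grades anything or shares the trial's hypothesis.
- *That a tilt could never be detected.* ESC-PTP and RF-CL are to be calculated for each subject, and the NICE inputs are baseline data for all. Both classes could be re-derived and compared with the recommendation.
- *That only NICE is exposed.* Pain type can switch the ESC class too; only the ECG part is specific to NICE.
- *That deferral makes the event impossible.* The panel sends a recommendation, and the article leaves major decisions to local physicians.

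**Conclusion.** The point holds in a limited form. As written, the decision that largely determines the primary endpoint is made by cardiologists who know the arm, and the described sequence does not prevent arm-aware handling of borderline chest pain or ECG calls. Bias is possible, not shown. Its size cannot be taken from the article: the 3.1–4.5 points rest on an assumed 5% tilt and an assumed 62–90% non-obstructive rate, and the 14% rejection rate on the assumptions of Illustration B. The results show that small shifts would matter, not that they will occur, and the direction could be either way. Because the exposure is avoidable at almost no cost, the sponsor should remove it.

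**What to change.** Amend Randomization and blinding so that:

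1. The blinded site investigator grades chest pain type and ECG on the baseline form, which is locked before the envelope is opened.
2. The risk group under both NICE and ESC is derived from that form by calculator or fixed rule, and both are recorded.
3. Opening the envelope only selects which recorded class is sent. The panel may not re-grade inputs or reclassify afterwards.

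The grading has to come from the locked site form. Reversing the panel's own two steps would not be enough, because with blocks of 2 it can predict every second allocation.

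The change alters no clinical rule and needs no extra tests or subjects. It costs a short text change, one extra form field and a few minutes per subject. It also gives a direct audit: every recommendation sent should equal the recorded class for the allocated strategy.
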